## Abstract

In Ghana, one in three adolescents are at risk of experiencing depression. However, access to treatment is limited due to the poor integration of mental health services into primary healthcare systems. Evidence-based interventions, especially psychological therapies and antidepressant medication, can restore health and functioning for depressed youth. Ghana currently runs a policy of free Senior High Secondary Education and aims to implement a national adolescent health policy. However, the mental health component is poorly developed. Our formative research informed the adaptation of a 6-session psychological intervention for depression, suitable for school-going youth aged 15-18 in Ghana.

The aim of this study is to conduct a pilot trial of this ‘African Youth in Mind’ (Y-MIND) intervention, to answer questions of feasibility and acceptability before evaluating the intervention in a larger definitive trial. The Y-MIND intervention blends evidence-based problem-solving therapy with behavioural activation and psychoeducation. The intervention will be delivered by trained and supervised guidance and counselling coordinators.

The study is a parallel arm cluster randomised controlled pilot trial. Six senior high schools will each be randomly allocated 2:1 to either the intervention condition or enhanced usual care (EUC). 60 adolescents aged 15 to 18 years in senior high schools who have scored have scored 10 or more on the locally validated Patient Health Questionnaire-9 (PHQ-9) will be randomised. The feasibility, acceptability and appropriateness of the intervention will be assessed using short quantitative measures, and qualitative interviews with adolescents and guidance and counselling coordinators. Symptoms of depression will be measured at 5 months post baseline assessment. Outcomes for anxiety, fidelity to the intervention, and cost effectiveness evaluation will also be collected.

This will be the first feasibility trial of a task-shifted psychological treatment (Y-MIND) for adolescents with depression delivered by Guidance and Counselling Coordinators in high schools in any African country.

Clinicaltrials.gov NCT06740084.

## Introduction

Depression is common in youth worldwide, preventing them from reaching their full educational, social and economic potential and increasing the risk of self-harm [1]. The majority of youth with depression in low- and middle-income countries do not receive treatment [2,3]. In Ghana, a significant portion of adolescents—one in three—are at risk of experiencing high depressive symptoms [4]. Despite the availability of mental health services across various levels of care, only a small fraction (26%) of young people utilize these services [4]. This low utilization is partly due to the poor integration of mental health services into primary healthcare systems [5,6]. Additionally, there is a lack of understanding regarding the mental health needs of young people and the treatment options available to them [5,6]. This highlights the need for improved mental health service delivery and awareness among young people in Ghana. In 2012, the Mental Health Act, Act 846 which focused on the creation, governance, and management of mental health services from the national to the district levels [7] was passed by the parliament of Ghana. However, the Act did not specify the programmes targeted at adolescents [5].

Evidence-based interventions, especially psychological therapies and antidepressant medication, can restore health and functioning for depressed youth [8,9]. However, psychological therapies, such as cognitive behavioural therapy, require skilled specialist cadres. Scarce resources in Ghana, like in most African countries, mean that there are few specialists with the skills or time to deliver psychological therapies. In Ghana, cognitive behavioural therapy (CBT), which requires the services of a highly trained psychologist, has not been culturally adapted for adolescents. Effective interventions for youth in high income countries cannot therefore simply translate into policy in Africa.

WHO policy for low-resource settings is that treatments for depression and other emotional disorders are integrated into existing health care facilities such as primary health care (PHC) and non-health care structures such as schools (Eaton et al., 2011; World Health Organization, 2016). Mental health officers, and those at hospitals that are close to schools, have been attempting to provide outreach mental health services within educational settings. However, these efforts have not proven to be effective because the numbers of mental health officers are still inadequate. In Ghana, the human resource in mental health is scare with the psychiatrist to patient ratio being 0.23/100,000 [10]. The implication is that access to mental health services is a challenge and therefore the health system has adopted the WHO task-shifting approach to bridge the gap in mental health services.

In Ghana, each district hospital is meant to have one trained psychologist but unlike in many high-income countries (HIC), psychological therapy is not readily available in primary care. Ghana currently runs a policy of free Senior High Secondary Education (FSHS). The policy has impacted positively on school enrollments and retention. Through schools, Ghana implements a pioneering national adolescent health policy. Mental health is listed as one of the Ghana school health packages [11], but is currently the least developed. Therefore, creating a friendly and mentally healthy school environment (strengthening guidance and counselling, improving the knowledge and skills of teachers who provide psychotherapy, incorporating basic education on mental health in the school curriculum) is timely and crucial in promoting the psychological well-being of adolescents in schools.

Our formative research informed the adaptation of a psychological intervention for depression, suitable for school-going youth aged 15-18 in Ghana. The work included a review of international clinical practice guidelines for depression in youth, a situation analysis, qualitative interviews with stakeholders including teachers, students, health care workers, and policy makers and participatory workshops with young people with lived experience of depression or anxiety to develop the intervention manual. Young people described depression as ‘thinking too much’ and ‘a heavy heart’ and this was common in situations of conflict, divorce or death of a parent, alcohol and drug use, low self-esteem, and financial constraints. Guidance and counselling coordinators within senior high schools were identified as the appropriate cadre to deliver the intervention. Key stakeholders also highlighted a preference for a one-on-one intervention delivered face to face. The adaptation of the intervention followed a modified version of the ADAPT-ITT framework for adaptation of behavioural interventions [12], taking in account context specific language and metaphors [13], and cultural concepts of distress [14]. The first draft of the adapted intervention was iteratively tested through a development case series.

Through this formative work, a 6-session one-to-one intervention for youth with depression was developed. This group now aim to conduct a pilot trial of this ‘African Youth in Mind’ (Y-MIND) intervention, to answer questions of feasibility and acceptability before evaluating the intervention in a larger definitive trial.

This protocol follows the ‘Standard Protocol Items: Recommendations for Interventional Trials’ (SPIRIT) reporting guidelines [15].

## Methods

This study was approved by King’s College London Research Ethics Committee (24^th^ June 2024, RESCM-23/24-38948), Ghana Health Services Research Ethics Committee (16^th^ July 2024, GHS-ERC:015/06/24), and the Navrongo Health Research Centre Research Institutional Review Board (3^rd^ July 2024, NHRCIRB480).

This study is registered at Clinicaltrials.gov (NCT06740084).

### Study design and setting

The study is a parallel arm cluster randomised controlled pilot trial. The unit of randomization will be clusters comprising Senior High Schools (SHS). The sampling frame will consist of all SHS (12 in number) in the Kassena-Nankana Municipal (KNM) and the Kassena-Nankana West District (KNWD), in the Upper East Region of Ghana. The districts are characterised by Guinea Savannah vegetation, with subsistence agriculture being the mainstay of the people. English language is the language of instruction, with Kassem and Nankani being the predominant s spoken languages in the settings. The KNWD hosts the Navrongo Health Research Centre (NHRC) which operates a demographic surveillance system that monitors the demographic dynamics of the populations (over 160,000) of both the KNM and the KNWD and facilitates tracking of study participants in longitudinal studies (Oduro et al., 2012).

Six SHSs will be selected based on the most populous schools. The six schools will each be randomly allocated 2:1 to either the intervention condition or enhanced usual care (EUC).

### Participant eligibility and recruitment procedures

Participants will be 1) Adolescents aged 15 to 18 years in senior high schools located within the Kassena-Nankana Municipality and Kassena-Nankana West District; 2) have scored 10 or more on the locally validated Patient Health Questionnaire-9 (PHQ-9) (Anum et al., 2019; Weobong et al., 2009); 3) be willing and able to be followed up for 5 months and; 4) provide informed consent or assent; For adolescents 15-17 years participants must have 5) access to a caregiver to obtain informed consent; 6) All participants must have the ability to read, write and communicate in English language.

Adolescents meeting inclusion criteria will be excluded if they 1) are currently receiving any psychological treatment (talking therapy) for any common mental disorder through formal health care services; 2) have active bipolar disorder or psychosis (assessed through a brief screening tool for bipolar disorder and psychosis); 3) have advanced or chronic physical illness (assessed through self-report); 4) have significant visual or hearing impairment which would interfere with their ability to take part in the study; or 5) are actively suicidal (assessed through the use of a four-item screening tool administered by a psychiatric nurse and reviewed by the trial clinical psychologist [16]).

### Screening and recruitment

We will conduct whole-school health education sessions in conjunction with the school health education programme. These sessions will include brief psychoeducation followed by an introduction to the Youth in Mind (Y-MIND) study using standardised information. If students are interested in the study after receiving information or following a whole-school psychoeducation session, they will first be invited to complete a brief screening tool to determine age and assess symptoms of depression using the Patient Health Questionnaire-2 (PHQ-2) [17]. The PHQ-2 is a two-item measure of symptoms of depression experience in the past two weeks. The measure is scored from zero to six [17]. A cut off of 3 or more will be used for this trial. This screening tool is designed to screen for students who are likely to meet the eligibility criteria (depression score of 10 or more using the Patient Health Questionnaire-9.

Young people who record a score of 3 or more on the PHQ-2 and meet the age criteria will be invited to complete informed consent procedures for the trial and participate in the eligibility and baseline assessments. A consent form will be signed by either the participant or his/her parent/guardian following a comprehensive and interactive explanation by research assistants trained to seek consent. Participants aged 18 will be invited to complete informed consent procedures and sign the consent form. For participants under the age of 18, assent will be obtained from the participant and consent will be sought from their guardian. This will be obtained through the school contacting their parent or caregiver to seek consent. The information sheet of the consent form will include all information on study procedures, potential risks and benefits of participation, privacy and confidentiality, compensation and whom they can contact for further information. It will also state that participation is voluntary, that participants can refuse to answer any question, that they can withdraw from the study at any time, and that if they decide not to participate in the study their care within the school will not be affected.

### Eligibility and baseline assessment

Participants will complete the eligibility and baseline assessments after giving informed consent. The eligibility and baseline assessment includes all measures for evaluation of inclusion and exclusion criteria, as described above.

The study team (Principal investigator(s) or designee, country lead or designee, project manager(s), and clinical psychologist(s)) will meet to discuss whether the participant meets entry criteria, before they are formally enrolled into the trial. This step will allow senior members of the research team to agree if potential participants meet all eligibility criteria, and have no exclusion criteria. See Fig 1. Schedule of enrolment, interventions, and assessments.

**Fig 1 pone.0319462.g001:**
[figure not shown]
Schedule of enrolment, interventions, and assessments.

Those agreed to be eligible will be invited to participate in the trial procedures. See Fig 2 flow diagram of trial procedures.

**Fig 2 pone.0319462.g002:**
[figure not shown]
Flow diagram of trial procedures.

### Randomisation

The six schools will each be randomly allocated 2:1 by simple randomisation to either the intervention condition or enhanced usual care (EUC) before screening and recruitment.

### Interventions

#### Enhanced usual care (EUC).

Our formative research showed that Guidance and Counselling Coordinators in the schools provide some counselling to students who need it. This includes counselling on stress during exams, poor academic results, and teenage pregnancy. Teachers also refer pupils to school nurses and/or to the locality health professionals. Building on the existing structure, usual care will be enhanced in three ways. 1) Teaching staff will receive basic training on common mental health conditions affecting youth in Ghana with an emphasis on depression and suicidal symptoms and treatment. The WHO guidelines for school health services will form the basis for the training for teachers [18]. 2) Nurses in all schools and other relevant local health care professionals will be trained in mental health, substance-use and self-harm including guidelines on when and where to refer young people for psychiatric care. The World Health Organization (WHO) Mental Health Gap intervention guide (mhGAP) (World Health Organization, 2015b) will be used for training of nurses and other health care professionals. 3) The study team will provide a letter to the Guidance and Counselling Coordinators for the participant. This will state their pupils’ score on the PHQ-9 and that scores of 10 and above indicate a possible diagnosis of depression.

### Youth in mind (Y-MIND) intervention

All participants in the intervention arm will receive the EUC (described above) plus the Y-MIND intervention. The Y-MIND intervention will be delivered by trained and supervised Guidance and Counselling Coordinators (GCC) at schools in 6 sessions. The first session will focus on psychoeducation on depression through storytelling to normalise the participant’s experiences of depression. After the psychoeducation the structure of the treatment is described and goals for therapy are agreed. Sessions 2 and 3 focus on helping the participant see the connection between their behaviour, daily activities, and low mood and activity scheduling. The GCC and participant agree specific and achievable goals based on participant’s interests, values, and preferences to promote active participation in activities that promote positive emotions and improve overall well-being. Sessions 4 and 5 focus on problem solving therapy, adapted from the Zimbabwean Friendship Bench (FB) intervention [19]. In these sessions, the GCC helps the participant identify and define a specific problem to work on, and break down problems into smaller components. The GCCand participant collaboratively brainstorm multiple possible solutions to the problem. The participant and GCC evaluate the potential solutions and consider their advantages, disadvantages, and feasibility together. The participant is encouraged to carry out the selected solution(s). In session 6 (last session) the GCC reviews the participant’s understanding of depression, including its symptoms and potential triggers to help participants recognise warning signs of relapse. Together, the GCC and participant work to create a personalized relapse prevention plan.

The PHQ-9 scores collected by the GCC at the beginning of each session will be collected for supervision purposes. If the participant’s PHQ-9 score has not changed this will be discussed in more detail with the Guidance and Counselling Coordinators and he/she will be provided with additional support from the clinical psychologist during the weekly supervision meetings.

### Incentives

All participants will receive incentives in line with local standards for attending research visits and in consultation with key stakeholders at the participating schools. In both arms participants will receive refreshments (a light snack) during the brief screening, refreshments and a notebook at the eligibility and baseline assessments participants, and refreshments and 2 bars of soap at the 5 month follow up visit. In the intervention arm participants will receive refreshments and 2 bars of soap during the intervention sessions. Participants invited to take part in an interview or group discussion will receive refreshments during the group discussion or interview.

### Outcomes

#### Primary outcomes.

Feasibility of the intervention, from the perspective of the adolescents, is defined as extent to which the Y-MIND intervention can be successfully delivered by Guidance and Counselling Coordinators to reduce symptoms of probable depression within senior high schools in Navrongo. Feasibility of the intervention will be measured using the ‘Feasibility of Intervention Measure’ (FIM) [20] with adolescents at the end of their last intervention session, (or at their 5 month follow up if the intervention session was not attended). The 4-item measure assesses the perceived degree to which interventions or programs are feasible and appropriate. The FIM is measured on a 5-point Likert scale ranging from completely disagree (scored as 1) to completely agree (scored as 5). Item scores are calculated as a mean score of the responses.

### Secondary outcomes

#### Feasibility outcomes.

Feasibility of conducting a fully powered trial evaluated through assessing the proportion of those eligible who consent, number of weeks to complete the intervention and feasibility of collecting clinical and self-report assessments at 5 months follow up.

Acceptability and appropriateness of the intervention will be measured using the Intervention Appropriateness Measure (IAM), Acceptability of Intervention Measure (AIM) [20] with adolescents at the end of their last intervention session (or at their 5 month follow up if the intervention session was not attended), and with Guidance and Counselling Coordinators at schools after they have finished delivering all intervention sessions. Acceptability will also be explored through interviews with adolescents and focus group discussions with Guidance and Counselling Coordinators to elicit feasibility, acceptability, appropriateness and barriers and or enablers that may influence the effectiveness of the intervention.

Feasibility of the intervention from the perspective of the Guidance and Counselling Coordinators, will also be measured using the Feasibility of Intervention Measure (FIM) [20] with Guidance and Counselling Coordinators after they have finished delivering all intervention sessions.

Fidelity to delivering the psychological intervention, defined as the extent to which the intervention was delivered as intended, and measured by rating 20% of randomly selected audio-recorded psychological intervention sessions in the experimental arm using a culturally adapted form of ENACT called the ‘Problem-Solving Therapy Fidelity Scale (PROOF)’ tool.

Fidelity of receipt of the intervention will be assessed through measuring the proportion of intervention sessions attended by adolescents, and the proportion of sessions in which homework was completed.

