### Measures for feasibility of conducting a fully powered trial

Feasibility of conducting a fully powered trial will be assessed by the number and proportion of adolescents screened using the brief screening tool, proportion of adolescents who complete the full eligibility assessment, proportion of adolescents eligible, number of weeks to complete the intervention and proportion of participants who complete follow up assessments at 5 months post baseline.

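### The consent outcome uses eligible students as its denominator, but eligibility is established only after consent, so as written it is 100% by construction

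*Protocol article*

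**What the plan says.** The Feasibility outcomes paragraph under Secondary outcomes says that the feasibility of a fully powered trial will be "evaluated through assessing the proportion of those eligible who consent", alongside the time taken to complete the intervention and the feasibility of collecting the 5-month assessments.

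The order of steps is set out elsewhere in the article:

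- **Screening and recruitment.** Students complete a short screen of age and PHQ-2. Of this screen the article says: "This screening tool is designed to screen for students who are likely to meet the eligibility criteria". Those who score 3 or more and meet the age criteria "will be invited to complete informed consent procedures for the trial and participate in the eligibility and baseline assessments". For those under 18, this means the student's assent plus a guardian's consent, sought through the school.
- **Eligibility and baseline assessment.** "Participants will complete the eligibility and baseline assessments after giving informed consent". On its content: "The eligibility and baseline assessment includes all measures for evaluation of inclusion and exclusion criteria, as described above". The study team then meets to agree who is eligible.
- **After that meeting.** "Those agreed to be eligible will be invited to participate in the trial procedures".
- **Participant eligibility and recruitment procedures.** The inclusion criteria include "4) provide informed consent or assent". For ages 15 to 17, criterion 5 adds access to a caregiver who can give consent.

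A second list, under Measures for feasibility of conducting a fully powered trial, has no consent proportion. It includes "proportion of adolescents who complete the full eligibility assessment, proportion of adolescents eligible".

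**The concern.** A proportion is informative only if its denominator can contain people who are not in its numerator. Here the denominator is eligible students and the numerator is those among them who consent. Eligibility is established only for students who have already consented. A student who declines, or whose guardian is not reached, has no PHQ-9 result and no exclusion checks, and so can never enter the denominator.

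Uptake is worth measuring in this pilot for three reasons. Guardian consent obtained through the school is an extra step for the 15 to 17 year olds and an obvious place to lose students. The sample is fixed at 10 per school, so reaching 60 does not show how many students had to be approached. Schools are allocated before screening and recruitment, so uptake could differ between arms, and a ratio fixed at 100% in both arms would not show it.

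**Working it through.** The article states no consent proportion, so there is no figure to reproduce. The check is one of logic, followed by an illustration of size.

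**1. Order of steps.** PHQ-2 and age screen → invitation to consent → consent, or assent plus guardian consent → PHQ-9 and exclusion checks → team agrees eligibility → invitation to trial procedures.

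**2. The ratio as written.** Let E be the number agreed to be eligible. Because eligibility is assessed after consent, all E have consented:

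ratio = (eligible and consented) / eligible = E / E = 100%.

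At the planned 60 participants this is 60/60, with an exact 95% lower limit of 0.025^(1/60) = 94.0%. Inclusion criterion 4 leads to the same place by another route: a student who does not consent or assent fails a criterion, so an eligible non-consenter cannot exist.

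**3. Setting criterion 4 aside.** Suppose R invited students do not consent. Anywhere from none to all of them might have met the other criteria, so consent among the truly eligible is only bounded, between 60/(60 + R) and 100%. R is assumed:

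| R | Lower bound |
|---|---|
| 10 | 60/70 = 86% |
| 25 | 60/85 = 71% |
| 50 | 60/110 = 55% |
| 100 | 60/160 = 38% |

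**4. The ratio with an observable denominator.** Use consented / invited, where invited means age-eligible with a PHQ-2 of 3 or more. The uptake and eligibility rates below are assumptions. If 60% of consenters prove eligible, 60/0.6 = 100 consenters are needed, and invited = 100/uptake.

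| Assumed uptake | Invited | Consented / invited (exact 95% CI) | Ratio as written |
|---|---|---|---|
| 40% | 250 | 40% (34 to 46) | 100% |
| 60% | 167 | 60% (52 to 67) | 100% |
| 80% | 125 | 80% (72 to 87) | 100% |
| 95% | 105 | 95% (89 to 98) | 100% |

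The eligibility assumption changes only the precision. At 60% uptake, with 40%, 60% or 80% of consenters eligible, the fractions are 150/250, 100/167 and 75/125, and the intervals are 54 to 66, 52 to 67 and 51 to 69.

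**5. What the second list would show.** If its completion proportion is taken over invited students and every consenter completes the assessment, the 60% row gives 100/167 = 60%, which is the uptake. If 10 consenters did not attend, it gives 90/167 = 54%, and the reader could not tell refusal from non-attendance. The article does not say which denominator applies.

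**The case against.** The strongest reply is that a consent problem would not be hidden. Consent is the gateway to the eligibility assessment, so a low proportion completing that assessment would reveal poor uptake, as step 5 shows. The Statistical methods section commits to reporting trial flow under CONSORT for cluster trials, and Table 1 lists a screening log and a recruitment log. This stands in part. A reader might infer that the pilot cannot detect a consent problem, or that it will misjudge how many students the definitive trial must approach. The full set of measures does not support either inference. What remains is that the completion proportion has no stated denominator and cannot separate its causes.

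A second reply is that the word eligible was meant loosely, as of the right age and PHQ-2 positive. The proportion would then be estimable and equal to the one proposed here. But the article describes these students only as likely to meet the criteria, and it places the measurement of the criteria after consent. If the loose sense is intended, the text has to say so.

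A third reply is that exact denominators are often left to the analysis plan. That would answer an omission. Here the article states a denominator, and it conflicts with the article's own procedures.

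The invitation that follows the eligibility decision does not rescue the ratio either. It could give a participation rate among the eligible, but it is not described as consent.

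Finally, caregiver access is itself a criterion for ages 15 to 17, so a student whose guardian cannot be reached is arguably ineligible and not a refuser. This is fair, and the fix has to keep the two apart.

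**Conclusion.** The point holds, at moderate severity. Followed as written, the consent proportion is 100% by construction and says nothing about uptake. This follows from the order of steps and from inclusion criterion 4, and it does not depend on the assumed counts. The second list of feasibility measures only partly fills the gap and does not agree with the first.

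The scope is narrow. This is one component of a secondary feasibility outcome, the article attaches no progression threshold to it, and the primary FIM outcome, the sample size and the clinical analyses are untouched. It should not be read as a failure of the pilot to collect what it needs. On the assumption that the two logs hold counts of students invited and consenting, the information exists and only the definition is wrong.

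**What to change.** In the Feasibility outcomes paragraph, redefine the consent rate as students with completed consent (age 18), or with both assent and guardian consent (ages 15 to 17), divided by all invited age-eligible students with a PHQ-2 of 3 or more. Then:

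- report eligible/consented and enrolled/eligible as separate steps;
- among those invited who did not consent, show refusals separately from guardians who could not be reached;
- state the denominator of the proportion completing the eligibility assessment;
- make the list under Measures for feasibility of conducting a fully powered trial match the list under Secondary outcomes.

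The Analysis of feasibility outcomes section already allows reporting by arm where appropriate, and that suits this rate. A breakdown by age group would be useful but is optional.

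The cost is a change of wording. Recruitment ran from 18 to 26 July 2024, so nothing in the conduct can change. The counts must come from the screening and recruitment logs, whose contents the article does not describe. If they do not record why consent was missing, the split between refusal and unreached guardians cannot be recovered from them, and the report should say so.
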